### Recruitment, randomization, and allocation concealment

#### Recruitment

Participants will be recruited through both online and on-site recruitment. The sample size calculation is based on the primary outcome: emergency preparedness of public for MEIDs. The sample size was performed using the formula developed by Chow [18], and the formula is as follows:$$\begin{array}{c}\mathrm{n}=2{\left(\sigma \frac{{z}_{1-\alpha /\left(2T\right)}+{z}_{1-\beta }}{{\mu }_{A}-{\mu }_{B}}\right)}^{2}\\ 1-\beta =\varphi \left(z-{z}_{1-\alpha /\left(2T\right)}\right)+{\varphi }\left(-z-{z}_{1-\alpha /\left(2T\right)}\right), z=\frac{{\mu }_{A}-{\mu }_{B}}{\sigma \sqrt{\frac{2}{n}} }\end{array}$$

The significance level of the test is α = 0.05, the test power is 1-β = 0.8, standard deviation is = 26.31, the number of comparisons to be made is T = 3, is the standard Normal distribution function. Calculator software (Power and Sample Size) was used to calculate the initial sample size N1 = 171. Considering the attrition rate of 20%, the sample size of each group was increased to 206, and the total sample size of the three groups was 618.

The study will be conducted in Luzhou City, Sichuan Province, China. Participants were recruited from the community and signed informed consent forms if they agreed to participate in the study and complete follow-up measurements. After completing the study, each participant will receive a reward of 50 RMB in cash.

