#### Randomization and allocation concealment

To reduce selection bias, randomization and allocation concealment are essential. To achieve randomization, there are the following steps: 1) Sequence numbers are drawn up for 618 participants; 2) 618 random numbers are randomly generated by computer; 3) 618 random numbers are finally distributed to 618 participants. Opaque envelopes are used to allocation concealment. In each of the 618 envelopes, each will contain a note with the words “The People’s War Against Pandemic intervention group 1” or “The People’s War Against Pandemic intervention group 2” or “Control group”(206 envelopes per group). Participants will randomly select an envelope in the order of random number and be assigned to the corresponding group according to the information in the envelope. The grouping information is saved by a third party. Unlinding is permissible when participants exit the research or statistical analysis is completed.

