### Data management and statistical analysis

Data will be collected, recorded and managed by the Survey Star, an online questionnaire platform (www.wjx.cn, Changsha Ranxing Information Technology Co., Ltd in China) to ensures the safety, integrity and consistency of the data. Researchers will download the data from Survey Star and save it in text format to a password-protected server. SPSS 21.0 analysis software was used for data analysis by the third party who did not participate in the intervention.

Data will be collected at baseline and descriptive statistics will be used to show the characteristics of each arm at baseline. The outcome indicator prevention and control knowledge of MEIDs is a binary variable, so the chi-square test will be used to compare among the three arms at the intervention completion, 1, 3, and 6 months after the intervention. Analysis of Variance (ANOVA) will be used to find out whether there are differences among the three arms in the outcome indicator-emergency preparedness of public for MEIDs. Repeated Measures ANOVA will be used to measure weather there are differences in emergency preparedness of public for MEIDs score at 1, 3, and 6 months after intervention. A Bonferroni correction will be used for multiple testing. Intention-to-treat analysis will be used to account for the influence of attrition. The difference was statistically significant when *P* ≤ 0. 05.

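### Bonferroni over the three pairwise comparisons is valid and already allowed for in the sample size, but Holm's step-down test keeps the same 5% family-wise error and can only add power: an optional gain, not an error

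*Protocol article*

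**What the plan says.** Under Data management and statistical analysis, the Protocol article compares emergency preparedness across the three arms by ANOVA, adds a repeated-measures ANOVA over follow-up, and then states: "A Bonferroni correction will be used for multiple testing". That sentence does not say which tests form the family.

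The family can be inferred from two other places. Study design lists three hypotheses, one for each pair of arms: no difference between intervention groups 1 and 2, and superiority of each over control. Recruitment sizes the trial with a normal quantile at 1 − α/(2T), where "the number of comparisons to be made is T = 3", and with these error rates: "The significance level of the test is α = 0.05, the test power is 1-β = 0.8". It also gives "standard deviation is = 26.31", and reports: "Calculator software (Power and Sample Size) was used to calculate the initial sample size N1 = 171". The text gives no value for the difference in means. The final size follows from "Considering the attrition rate of 20%, the sample size of each group was increased to 206".

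**The concern.** Under plain Bonferroni each pair is tested at 0.05/3, whatever the other two pairs show. One of the three is group 1 versus group 2, where hypothesis 1 expects no difference. The share of the error rate set aside for that pair can never be passed on to the two comparisons with control, even after one of them has been rejected.

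Step-down tests do pass it on. Holm tests the smallest p-value at 0.05/3, the next at 0.05/2 and the last at 0.05, and stops at the first non-rejection. It controls family-wise error under any dependence and rejects everything that Bonferroni rejects. With exactly three means, one unequal pair implies that at least one other pair is unequal too. Once one null hypothesis is false, therefore, at most one of the others can be true. Shaffer's version uses this to test both remaining pairs at 0.05 after the first rejection. Hypotheses 2 and 3 are separate claims, each needing its own rejection, so what is at stake is the chance of establishing the second after the first.

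**Working it through.** **Inputs.** From Recruitment: α = 0.05, power 0.80, T = 3, SD 26.31, 171 per arm before attrition, 20% attrition, 206 per arm after. Equal allocation is from Randomization and allocation concealment ("206 envelopes per group"). The mean difference is an assumption, because the text does not give it.

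**The plan's own figure.** The formula is n = 2·[σ(z₁₋α/(2T) + z₁₋β)/Δ]². The quantiles are z at 1 − 0.05/6 = 2.394 and z at 0.80 = 0.8416. Solving for Δ at n = 171 gives 26.31 × √(2/171) × (2.394 + 0.8416) = 9.21, or 0.35 SD. Forward check: 2 × (3.2356/0.35)² = 170.9, rounded up to 171. So 171 agrees with a difference of 0.35 SD, but cannot be confirmed independently.

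**Power under the three procedures.** Simulation of three arms with pooled-variance t tests, groups 1 and 2 equal and both better than control, as the protocol's hypotheses expect:

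| Per arm | Difference | Quantity | Bonferroni | Holm | Shaffer |
|---|---|---|---|---|---|
| 171 | 0.35 SD | each comparison with control | 0.80 | 0.83 | 0.86 |
| 171 | 0.35 SD | both comparisons with control | 0.68 | 0.74 | 0.81 |
| 171 | 0.35 SD | at least one rejection | 0.91 | 0.91 | 0.91 |
| 171 | 0.35 SD | false rejection, group 1 v group 2 | 0.017 | 0.037 | 0.049 |
| 171 | 0.30 SD | both comparisons with control | 0.49 | 0.56 | 0.65 |
| 171 | 0.40 SD | both comparisons with control | 0.84 | 0.88 | 0.92 |
| 171 | 0.50 SD | both comparisons with control | 0.98 | 0.985 | 0.99 |
| 165 | 0.35 SD | each comparison with control | 0.78 | 0.81 | 0.85 |
| 165 | 0.35 SD | both comparisons with control | 0.66 | 0.72 | 0.80 |

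With all arms equal at 171 per arm, family-wise error is 0.044 for each procedure. Known-variance z tests give nearly the same joint power at 0.35 SD: 0.69, 0.74 and 0.81. In one million z-test trials no Bonferroni rejection was missed by Holm, and Holm added a rejection in 7.3% of trials.

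**Where 165 comes from.** 206 × 0.80 = 164.8. The 206 is 171 × 1.20 = 205.2, rounded up, whereas division by 0.80 would give 214. The fall from 0.80 to 0.78 under Bonferroni at 165 comes from that inflation step and not from the choice of correction.

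**The case against.** The strongest reply is that nothing here is wrong. Bonferroni is valid and prespecified, and it is the correction for which the trial was sized. Its cost is already in the 171, and at 171 every comparison has its 80%. That stands in full.

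A reader might infer that the trial falls short of its stated power, because the chance of establishing both hypotheses 2 and 3 is only 0.68. The document does not support this. Its formula gives 80% for a single comparison, and nowhere does it promise 80% for the two jointly. The joint figure shows where a step-down test helps, not a missed target.

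A reader might also infer that the gain is free. It is not quite. Step-down tests have no simple matching simultaneous intervals, whereas Bonferroni does. The group 1 versus group 2 comparison, which the Discussion uses to judge training duration, is also tested more liberally: its false-rejection rate more than doubles under Holm and nearly triples under Shaffer, though it stays within 5%.

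Two further points stand. The quoted sentence does not name its family, so it may also be meant to cover outcomes or time points. A replacement that spoke only of three pairs would delete that protection, and one tied to a primary time point would rest on something this document does not name. Lastly, Shaffer is not the most powerful option either: a closed test gated by the ANOVA reached 0.88 per comparison and 0.83 for both in the z-test simulation. The choice is among valid methods.

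**Conclusion.** The point holds as an optional efficiency gain and not as an error in the plan. For the three pairwise comparisons, Holm or Shaffer rejects at least as many hypotheses as Bonferroni at the same 5% family-wise level, with no added assumption about dependence.

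At 171 per arm and 0.35 SD, the gain in power to win both comparisons with control is about 6 percentage points with Holm and 13 with Shaffer. Per comparison it is about 3 and 6. At 165 per arm, either procedure brings power per comparison back above 80%. Nothing is gained for the first rejection.

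These sizes rest on three assumptions: that the family is the three pairs, as T = 3 and the three hypotheses suggest; that the two intervention groups are equally effective; and that the difference is about 0.35 SD, which is back-solved. The ordering of the procedures does not depend on the effect size, but the size of the gain does, and by 0.50 SD it has almost gone.

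**What to change.** Before outcome data are seen, the sponsor could state that the three pairwise comparisons of emergency preparedness, at each time point where they are made, are tested with Holm's procedure at two-sided family-wise 5%, with Shaffer's modification for three groups optional. The text should name those three pairs as the family and leave in place any correction intended across other outcomes or time points. The T = 3 sample size can stay as a conservative calculation.

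The cost is a short edit to the analysis section. No further participants are needed, and the step-down decisions can be worked out by hand from unadjusted SPSS p-values. Where simultaneous intervals are wanted, report Bonferroni intervals alongside and say that they may not match the step-down result. The higher false-rejection rate for group 1 versus group 2 should be accepted knowingly. If the sponsor prefers matching intervals or the stricter test of that pair, keeping Bonferroni is defensible.

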### Trial registration

This study was funded in 2021 and registered in the Chinese Clinical Trial Registry (registration number: ChiCTR2200060919) in June 2022. Recruitment and enrollment of participants began in July 2022.

### Dissemination policy

The results will be disseminated in the form of a paper or research report. After testing and review, The People’s War Against Pandemic will be provided to public free of charge online. The original data will be uploaded to the China Clinical Trial Registry, where the original data can be viewed by searching the study registration number.

## Discussion

WHO encourages individuals to be educated in the necessary knowledge and skills related to emergency preparedness, especially in areas where emergency preparedness is weak [19]. In the pandemic of a MEID, the emergency preparedness of public was not enough to support the public's response and recovery [20]. On the one hand, the public usually receives publicity on emergency knowledge, emergency skills and preventive measures of MEIDs in daily life [21], and lacks emergency preparedness education on social cooperation, legal compliance, economic estimation, material reserves and physical and mental health. On the other hand, the evaluation indicators of emergency preparedness for MEIDs in China pay more attention to the preparation of knowledge and ability but ignore the preparation of emotion and behavior tendency [22]. This study provides the public with a panoramic understanding of the response to MEIDs, to promote their comprehensive preparation and finally achieve an effective response.

To meet the educational need of emergency preparedness of MEIDs for public, a virtual interactive training system The People’s War Against Pandemic was developed. As mentioned above, The People’s War Against Pandemic is a theory-based virtual interactive training system that can provide emergency knowledge, emergency skills, preventive measures, emergency emotion and behavior tendency to public to response and recover from MEIDs. Whether public are interested in The People’s War Against Pandemic and insist on using it is the key to improve the emergency preparedness of public. If the virtual interactive training system does not appeal to public, it will not be popularized among them, nor have educational significance. To promote the use of the virtual interactive training system by public, some elements are used to design the system, including storylines, virtual scenes, and interactions and scoring. This research realizes the interaction between human and computer by publishing tasks, independent selection and timely feedback. Compared with other training systems [23]. The People’s War Against Pandemic supports users to choose by themselves at the interactive node to determine the direction of training, which can mobilize users' subjective initiative and stimulate their learning motivation.

Three arms were designed in this research, including two intervention arms and one control arms. Participants in the two intervention groups will receive The People’s War Against Pandemic to complete the storyline task at least once a day, read at least one article and watch one video in the knowledge corner, and complete a retest of wrong choices in the intelligent evaluation module. The difference between the two groups is the intervention time. Due to the interactivity of virtual interactive training system, participants may have different outcomes in different training. To explore the optimal duration to finish all the outcomes, we designed two-week and four-week groups, so that the participants will neither fail to achieve the training effect due to too short time nor get bored due to too long time. By comparing the intervention groups with the control group, it can be found whether The People’s War Against Pandemic is better than autonomous learning in improving emergency preparedness of MEIDs for public. By comparing the two intervention groups, we can find out the optimal duration to improve emergency preparedness of MEIDs for public.

### Limitations

As with any research design, the trial also has potential limitations. In the follow-up observation, the time may be too long, to loss of participants. We can reduce the dropout rate by strengthening the connection with participants or giving appropriate rewards. In addition, The People’s War Against Pandemic has a scoring element, and participants may be addicted to pursuing high scores. To address this problem, we can limit the time of training every day.

## Data Availability

Not applicable.

## Abbreviations

MEIDs: Major emerging infectious diseases
COVID-19: Corona virus disease 2019
I-CVI: Item-level content validity index
S-CVI: Scale-level content validity index
ANOVA: Analysis of Variance
